## Abstract

**Background:**

Hope is defined by caregivers as the inner strength to achieve future good and to continue care giving. Pilot test findings of a Living with Hope Program (LWHP) suggested it is an acceptable and feasible intervention for use by family caregivers. Although it shows promise in potentially increasing hope and quality of life, further testing and development is needed. Questions remain as to: a) what are the mechanisms through which the LWHP affects outcomes and b) how long it is effective? *The overall purpose of this time series mixed method study is the further development and testing of the LWHP by*:

a. Determining the mechanisms of the LWHP by testing a LWHP conceptual model in which self-efficacy, and loss/grief are hypothesized intermediary variables for changes in hope, and subsequently quality of life among rural women caring for persons with advanced cancer, and;

b. Exploring the longitudinal effects of the LWHP on hope, quality of life and health services utilization among rural women caring for persons with advanced cancer.

**Methods/Design:**

Using a time-series embedded mixed method design, data will be collected from 200 rural women caregivers. Following the collection of baseline and outcome variables, the intervention (LWHP) is applied to all subjects. Subjects are followed over time with repeated measures of outcome variables (1 wk, 2 wk, 3, 6 and 12 months). The journals that are completed as part of the LWHP comprise the qualitative data. Health services utilization data will be collected from the Saskatchewan Health Administrative Database for all subjects one year prior and one year after study enrolment.

Path analysis will be used to test the model post LWHP, at 1 and 2 weeks. Two-factor ANCOVA will determine patterns over time and Cortazzi's narrative analysis will be used to analyze subjects journals completed as part of the LWHP.

**Discussion:**

Data Collection began January 2009 and is expected to be completed within 2 years time. Monthly meetings with data collectors and site collaborators have been instrumental in revisions to the original study protocol such as identifying and adding additional study sites.

**Trial Registration:**

Trial Registration; Clinical Trials.Gov. NCT01081301

## Background

More than a million Canadians need support to care for dying family members. This number will increase as the population of seniors in Canada will grow 33% by 2020[1]. Thus there is an urgent need for effective supportive interventions for caregivers of terminally ill family members given the dearth of research in this area[2]. Psychosocial supportive hope programs have been found to increase quality of life and improve the personal health of persons with advanced cancer[3]. Since hope has been identified as a key psychosocial resource among family caregivers to manage and deal with the caregiver experience [4-6] it is hypothesized that they may also benefit from a hope-focused intervention tailored to their needs. Hope is defined by caregivers as the inner strength to achieve future good and to continue care giving[4]. The goal of the Canadian Institutes of Health Research funded study protocol described below is to evaluate and further develop a Living with Hope Program (LWHP) for rural women caregiving for a person with advanced cancer.

The LWHP is a self-administered hope program that consists of watching an international award winning Living with Hope video followed by a 2 week hope activity. A pilot study funded by the Canadian Institutes of Health Region evaluated its ease and feasibility of use[7]. It was conducted in a rural health region in southern Saskatchewan. Ten family caregivers of terminally ill patients participated in the pilot. Data collection included baseline and post scores at 1 and 2 weeks of hope [Herth Hope Index (HHI)] [8] and quality of life [Quality of Life in Life Threatening Illness-Family Caregiver (QOLLTI-F)] [9]. Study participants completed 101 journal entries over a two -week time period. On average the participants completed 5.5 journal entries per week and spent on average 9.28 minutes per journal entry. The qualitative data suggested that the LWHP was effective in increasing the participants' hope and quality of life. Using a qualitative evaluation tool, subjects positively evaluated the study procedures including the video and journaling.

The LWHP was developed based on a grounded theory study of the hope experience of family caregivers [4]. This substantive theory was further developed based on additional hope research by the team and others, and is the conceptual framework for the current study. In this theory, hope is viewed as a dynamic inner strength that is a psychological resource for family caregivers to deal with the caregiving experience. Family caregivers go through the processes of living in the moment, being positive (cognitive reframing), and writing their own story (perceptions of control) so that they can live with hope.

The theory was used to determine the critical inputs of the LWHP. Critical inputs address the nature of the intervention in terms of what is necessary to produce the expected effects [10]. The critical inputs for the LWHP were watching the LWH video followed by 2 weeks of guided journaling. The Living with Hope video illustrates terminally ill persons and their family members talking about how they maintain their hope. One of the strongest benefits of videotaped presentations is the video modeling which occurs when viewers identify with the individuals on the videotape and perceive themselves as capable of performing specific task [11,12]. Journaling has been found to help individuals cognitively organize stressful events [13]. The instructions for the LWHP journal writing facilitate the cognitive organizing of the caregivers' challenges, including a cognitive reframing of what gave them hope.

The theory "Hanging on to Hope" incorporates concepts from Social Cognitive Theory [14] which were perceptions of control or perceived self-efficacy (writing their own story) and cognitive reframing (being positive). The belief that they could change their hope (self-efficacy) and cognitive reframing are components of Social Cognitive Theory (SCT). In a meta-analysis of psychosocial intervention components, Graves found those interventions with SCT components were effective in improving quality of life scores [15]. In particular those interventions focusing on increasing self-efficacy, the belief in their ability to organize and execute actions, have an influence on a person's psychological and physiological functioning (health status) [14]. Thus, the team hypothesized that hope may have an impact on quality of life [16], with quality of life (subjective well being), in turn, having an influence on health services utilization of caregivers [17]. Based on the review of the scientific hope literature, together with the "Hanging on to Hope" and Social Cognitive theory, the proposed study's conceptual framework is presented in Figure 1.

**Figure 1 F1:**
[figure not shown]
**Living With Hope Program Conceptual Model**.

Pilot test findings suggested the LWHP is an acceptable and feasible intervention for use by family caregivers [7]. Although it shows promise in potentially increasing hope and quality of life, further testing and development is needed. Questions remain as to: a) what are the mechanisms through which the LWHP affects outcomes, and b) how long is it effective?

### Purpose

The overall purpose of this time series mixed method study is the further development and testing of the LWHP by:

a) Determining the mechanisms of the LWHP by testing the LWHP conceptual model (Figure 1), in which 2 variables (self-efficacy and loss/grief) are hypothesized as intermediary variables for changes in hope and subsequently quality of life among rural women caring for persons with advanced cancer. We hypothesize that the administration of the LWHP will improve self-efficacy and decrease feelings of loss/grief. This will lead to a positive influence on the proximal outcome of hope and the distal outcome of quality of life. The functional status of the care recipient is hypothesized to have a moderating effect on all outcome variables. Understanding the change mechanisms or processes associated with interventions is an important step in their refinement and provides insight into the development of state of the art psychosocial interventions [15].

b) Exploring the longitudinal effects of the LWHP on hope, quality of life and health services utilization among rural women caring for persons with advanced cancer. This study is unique, as it will follow caregivers over a one-year period. The team will explore if the LWHP has benefits beyond what was found in the completed pilot study (1 and 2 weeks) by: a) comparing baseline scores of hope and quality of life to scores after the LWHP over time (3, 6 and 12 months) and b) comparing the number of physician visits and prescriptions one year prior to one year post LWHP. Approximately 50% of study subjects will become bereaved one month after study enrolment; rather than dropping bereaved caregivers from the study, the team believes these subjects will add to the understanding of hope, quality of life and health care utilization among caregivers. Thus these subjects will be retained if possible and followed through bereavement. In this way patterns of hope, quality of life and health care services utilization will be delineated over time for active and bereaved caregivers.

Justification for Focus on Rural Women:

Most informal caregivers in Canada are women, usually wives, daughters and daughters in-law [18-21]. Women caring for dying persons at the end of life have been identified in the literature as those most likely to experience negative physical and mental health outcomes, such as declines in health status, depression and anxiety from caregiver burden [20]. Caregivers have also identified benefits to caregiving. Given these benefits it is important to support women in their care giving role [22]. Family caregivers who do not have access to palliative services including counselling and bereavement services, such as those living in rural areas, are in need of more support than other populations [18].

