### Specific Aims and Hypotheses

Table 1 outlines the operationalization of the study concepts (measures) based on the LWHP conceptual model. The research team based the decisions for the variables being studied on the LWHP conceptual framework. We also considered which measures could be used given that subjects would become bereaved and minimal burden of data collection to all subjects was a chief consideration.

**Table 1 T1:** Variables and Measures

Variables	Caregivers/measures	Bereaved Caregivers/measures
Hope	Herth Hope Index (HHI)	Herth Hope Index (HHI)

Self Efficacy	General Self Efficacy Scale (GSE)	General Self Efficacy Scale (GSE)

Grief/Loss	Non Death Version of the Revised Grief Experience Inventory (ND RGEI)	Revised Grief Experience Inventory (RGEI)

Quality of Life	Short Form 12 Quality of Life Questionnaire Version 2 (SF12) Palliative Performance Scale (PPS) for family member with advanced cancer	Short Form 12 Quality of Life Questionnaire Version 2(SF12)

Health Services Utilization	# of physicians visit and prescriptions one year after study enrolment minus one year prior.	# of physicians visit and prescriptions one year after study enrolment minus one year after.

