### Specific Aim #1

Hypothesis #1.1 (testing of the model) will be tested with path analysis modeling. Path Analysis is a multivariate statistical technique in which a series of multiple regression models are used to test the strength of the influence, and by implication, the causal relationships between variables. Change scores will be calculated by post intervention minus baseline scores. Variables will be assessed for multi-co linearity and association. Those variables that are significantly correlated with the outcome variables will be entered into the path analysis model. Possible mediator variables such as Palliative Performance Scale (PPS) and significantly correlated caregiver demographics will be co-variants. Path Analysis will be used to test the model at 1 and 2 weeks.

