### Specific Aim #3

Hypothesis #3.1 (patterns of GSE, RGEI/NGREGI, HHI, SF12 and HSU over time) will be tested by repeated measures 2- factor ANCOVA with between groups factor (non-bereaved versus bereaved) and a repeated-measures factor for time (3, 6, and 12 months) to describe the patterns of the scores over time. PPS and caregiver demographics that were significantly correlated will be co-variants. If the F scores are significant (p < .05) post hoc testing will be done to determine where the scores are significantly different.

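### Functional status (PPS) is hypothesised as a moderator, but the plan calls it a mediator and enters it only as a covariate, so no planned term tests moderation of the model's paths

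*Protocol article*

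**What the plan says.** The protocol article gives PPS three roles.

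- **Moderator.** Purpose, item a: "The functional status of the care recipient is hypothesized to have a moderating effect on all outcome variables". The same paragraph reserves the intermediary role for two other variables: "2 variables (self-efficacy and loss/grief) are hypothesized as intermediary variables".
- **Mediator and covariate.** Data Analysis, Specific Aim #1: "Possible mediator variables such as Palliative Performance Scale (PPS) and significantly correlated caregiver demographics will be co-variants". The sentence just before it sets a general entry rule: "Those variables that are significantly correlated with the outcome variables will be entered into the path analysis model". The outcomes are differences from baseline: "Change scores will be calculated by post intervention minus baseline scores".
- **Covariate.** Data Analysis, Specific Aim #3: "PPS and caregiver demographics that were significantly correlated will be co-variants". No time point is given for this PPS. The model compares bereaved with non-bereaved caregivers at 3, 6 and 12 months.

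On availability, Table 1 (Specific Aims and Hypotheses) lists "Palliative Performance Scale (PPS) for family member with advanced cancer" in the column for active caregivers and not in the column for bereaved caregivers. The Data Collection section, however, has the research assistant assign a PPS at the first visit, before the programme starts, and repeats the first-visit measures (except demographics) at visits two to six.

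**The concern.** A moderator changes the strength of a relation between two other variables, and a regression shows this through a product term or a stratified fit. A mediator lies on the causal route from intervention to outcome. A covariate shifts the level of the outcome. These are three different models, and the one that the plan describes is not the one that its hypothesis needs. Neither numbered hypothesis (1.1, 3.1) and neither analysis section names a PPS product term or a stratified analysis.

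The stated purpose of Aim 1 is to test the conceptual model, and the Methods/Design section says that the theory and the programme will be revised if the findings do not support it. A part of the model without a matching test cannot inform that decision. A null PPS covariate, or a PPS that fails the correlation screen, could be read as evidence against moderation when it says almost nothing about it.

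In Aim 3 the open question is which PPS is meant. After the care recipient has died there is no current value to use.

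**Working it through.** **1. The plan's own figure.** The Sample Size paragraph asks for 98 subjects for six variables at alpha 0.05 and power 0.80. The effect size is not stated; f² = 0.15 is assumed here. For the overall F test with u predictors, v = N − u − 1 and λ = f²N. With u = 6 and N = 98, v = 91 and λ = 0.15 × 98 = 14.7, which gives power 0.804 (0.798 at N = 97). The figure of 98 is reproduced. The six variables are self-efficacy, grief, hope, quality of life, physician visits and prescriptions. Neither PPS nor any product term is counted.

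**2. The same test with PPS added (f² = 0.15).** With PPS (7 predictors), N = 103. With PPS and two product terms (9 predictors), N = 114, and 98 subjects then give power 0.72. Both sizes lie below the planned 200.

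**3. What the covariate coefficient measures.** Let Y be the change in hope, S self-efficacy (or grief) and P the PPS:

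Y = b0 + b1·S + b2·P + b3·S·P + error

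The effect of S on Y is b1 + b3·P, so moderation of the path means b3 ≠ 0. If the product is left out and S and P are independent, the coefficient of P estimates b2 + b3·E(S). When S is centred, E(S) = 0 and b3 drops out.

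**4. Simulation of pure moderation.** Y = 0.3·S + √f²·S·P + error, with S, P and error independent standard normal and 4,000 runs per row. Share of runs significant at about the 5% level:

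| N | assumed f² | PPS as covariate | PPS passes correlation screen | product term |
|---|---|---|---|---|
| 98 | 0.02 | 6% | 6% | 28% |
| 98 | 0.05 | 7% | 6% | 55% |
| 98 | 0.15 | 8% | 8% | 94% |
| 200 | 0.02 | 5% | 5% | 50% |
| 200 | 0.05 | 6% | 6% | 86% |
| 200 | 0.15 | 8% | 8% | 100% |

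The covariate and the screen stay near the error rate even when moderation is strong.

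**5. Power of the proposed test.** Partial F test of the two product terms (2 df, 9 predictors in all, λ = f²N):

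| assumed interaction f² | λ at N = 200 | power at 98 | power at 200 | N for power 0.80 |
|---|---|---|---|---|
| 0.02 | 4 | 0.22 | 0.41 | 485 |
| 0.05 | 10 | 0.48 | 0.81 | 196 |
| 0.15 | 30 | 0.93 | over 0.99 | 68 |

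**6. Which PPS exists in Aim 3.** The Sample Size paragraph cites palliative home care data with 75% of patients dead by day 82.75. Applied to 200 subjects, 0.75 × 200 = 150 would be bereaved by then. That leaves at most about 200 − 150 = 50 with a current PPS at 3 months. A baseline PPS is planned for all 200.

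**The case against.** The strongest case on the other side has four parts.

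- **Moderation is examined after all.** Everyone receives the programme and the outcome is a change score, so a PPS coefficient asks whether change differs by functional status. This stands in part, and a reader who infers that moderation is never tested in any form goes too far. But it is a weak, uncontrolled test, the plan does not present it as a test of moderation, and by step 3 it does not address the self-efficacy and grief paths.
- **The Purpose speaks of outcome variables, not paths.** Figure 1, which could not be read for this check, may show which relations PPS is meant to moderate, and PPS appears in neither numbered hypothesis. This lowers the weight of the point. It does not reconcile moderator with mediator.
- **Aim 3 is sound if baseline PPS is meant.** This stands. From Table 1 a reader might infer that bereaved caregivers have no PPS and that the Aim 3 model therefore loses the whole group. The documents do not support that: every subject gets a PPS at the first visit, no time point is fixed for the covariate, and the Data Analysis section provides for regression prediction of missing scores, not deletion of cases. Nor does any section score PPS as zero after death, so a claim that PPS would duplicate the bereavement factor describes an analysis that the plan does not contain.
- **Such detail belongs in a fuller plan.** That would excuse silence. Here the article states the role of PPS, and states it inconsistently.

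**Conclusion.** The contradiction between hypothesis and analysis is established from the text alone. As written, no term tests whether PPS modifies the self-efficacy or grief paths to hope and quality of life. The correlation screen, which contains no stated exemption for PPS, could also keep it out of the model altogether.

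The size of the loss rests on assumed interaction effects (f² 0.02 to 0.15), independent normal variables and a centred predictor. If the mean of S is not zero, the covariate picks up part of the interaction, but mixed with the PPS main effect and so not separable from it.

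In Aim 3 the defect is narrower: the time point of PPS is not fixed. A concurrent value would have to be imputed for care recipients who have died, or would remove the bereaved group that Hypothesis 3.1 compares. The count of about 50 assumes that the cited regional home care death rates apply to this sample, which also recruits from cancer clinics. The point should be corrected; it does not undermine the study as a whole.

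**What to change.** **Data Analysis, Specific Aim #1.** Replace mediator with moderator for PPS. Always include the baseline PPS main effect, exempt from the correlation screen. Add pre-specified centred baseline PPS × self-efficacy and PPS × grief terms to the hope and quality-of-life equations, test them jointly, and label the test exploratory.

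Also align the Purpose sentence with these two equations. Because every subject receives the programme, no product of PPS with the intervention can be formed, and a claim about all outcome variables reaches further than the design can test.

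**Data Analysis, Specific Aim #3.** Name baseline PPS as the covariate.

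**Cost.** No new data are needed. Each equation gains two terms, and power for them is modest unless the interaction is at least moderate (step 5). A non-significant result should therefore be reported with confidence intervals and not as absence of moderation.

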### Specific Aims and Hypotheses

Table 1 outlines the operationalization of the study concepts (measures) based on the LWHP conceptual model. The research team based the decisions for the variables being studied on the LWHP conceptual framework. We also considered which measures could be used given that subjects would become bereaved and minimal burden of data collection to all subjects was a chief consideration.

**Table 1 T1:** Variables and Measures

Variables	Caregivers/measures	Bereaved Caregivers/measures
Hope	Herth Hope Index (HHI)	Herth Hope Index (HHI)

Self Efficacy	General Self Efficacy Scale (GSE)	General Self Efficacy Scale (GSE)

Grief/Loss	Non Death Version of the Revised Grief Experience Inventory (ND RGEI)	Revised Grief Experience Inventory (RGEI)

Quality of Life	Short Form 12 Quality of Life Questionnaire Version 2 (SF12) Palliative Performance Scale (PPS) for family member with advanced cancer	Short Form 12 Quality of Life Questionnaire Version 2(SF12)

Health Services Utilization	# of physicians visit and prescriptions one year after study enrolment minus one year prior.	# of physicians visit and prescriptions one year after study enrolment minus one year after.

### Specific Aim #1

To determine the mechanisms of the LWHP by testing the LWHP conceptual model (Figure 1), by examining if, at 1 and 2 weeks post LWHP compared to baseline, self-efficacy [General Self-Efficacy Scale (GSE)] and Loss and Grief [Revised Grief Inventory (RGEI) or NonDeath RGEI (NDRGEI)] scores predict changes in hope [Herth Hope Index (HHI) Factor 1] and quality of life [SF12 V2 mental health sub score-MHS (MHS-SF12)] scores for rural women caring for persons with advanced cancer.

1.1 Main Hypothesis: The subjects' general self efficacy and loss and grief (RGEI/NDRGEI) scores will significantly predict the HHI (Factor 1) score and the mental health score on the SF12 V2 at 1 and 2 weeks.

### Specific Aim #2

To describe the participants' perception of what fosters their hope.

2.1 Research Question: What do the study participants describe in their journals that fosters their hope?

### Specific Aim #3

To explore the longitudinal effects of the LWHP on hope, quality of life and health services utilization among rural women caring for persons with advanced cancer by describing the patterns of change scores from base line in hope, general self efficacy, loss/grief and quality of life in rural women caring for persons with advanced cancer and those who become bereaved at 3, 6 and 12 months. The time frames are based on Herth's [16] intervention study in which increases in hope scores were significant at 3, 6 and 12 months and in bereavement studies where effects of bereavement on health are shown to last up to a year [23]. Patterns of change in health services utilization (the number of prescriptions and physicians' visits one year prior compared to one year post LWHP) (HSU) will also be described. From the literature and Holtslander and Duggleby's [24] qualitative study of hope and bereavement, we hypothesized that the patterns of change will be different for active compared to bereaved caregivers, but the direction is unknown as no studies have reported these patterns.

3.1 Hypothesis: Following the LWHP, the pattern of change in scores (GSE, RGEI/NDRGEI, HHI, and SF 12 V2) from baseline will be significantly different for active than for bereaved caregivers at 3, 6 and 12 months.

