## Methods/Design

A time-series embedded mixed method design will be used to achieve the study purpose and aims. In a time series design, baseline and outcome variables are measured, the intervention (LWHP) is applied to all subjects, and they are followed over time with repeated measures of outcome variables [25]. A time series design was chosen instead of an experimental design because the purpose of the proposed research is to explore the mechanisms or causal processes of the LWHP. This is accomplished through path analysis in which experimental designs are not typically used [26]. The time series design was also chosen because of the ethical issues of assigning subjects to a control group when the intervention has shown potential benefits. In the pilot study of the LWHP, qualitative data suggests that the LWHP has positive benefits [7]. Harding and Higginson [27], in a systematic review of interventions in palliative care suggested that interventions should be evaluated using repeated measures from baseline and that ideal randomized controlled trials (RCT) may be inappropriate. These design recommendations were supported by Grande and Todd [28] following their review of RCTs in palliative care research. Grande and Todd also recommended using mixed method designs (quantitative and qualitative) to improve interpretation of the results.

Baseline hope, quality of life, loss/grief, and self-efficacy data will be collected before the subjects receive the LWHP. These measures will then be repeated at 1 and 2 weeks, 3, 6, and 12 months. Health services utilization data will be collected from the Saskatchewan Health Administrative Database for all subjects one year prior and one year after study enrolment.

One aspect of the LWHP asks subjects to keep a journal of their challenges and what gave them hope each day. This narrative qualitative data will be collected for the first 2 weeks as part of the intervention and analyzed to inform the quantitative data regarding the mechanisms involved in the LWHP. In this way, the collection of the qualitative data will not interfere with the LWHP mechanisms but inform it. The quantitative and qualitative data are collected concurrently with the quantitative being the predominant design to gain perspectives from the different types of data [29].

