### Setting and Sample

This study is being conducted in the homes of rural women caring for persons with advanced cancer receiving services from the Saskatchewan Cancer Agency ambulatory clinics in Saskatoon and Regina and those receiving home care in the Sunrise and Regina Qu'Appelle Health Region. Women who are caregiving are a family member or significant other identified by the patient as a primary source of emotional and physical support.

Inclusion and exclusion criteria: Sample inclusion criteria for the study will be: a) female, b) 18 years of age and older, c) caring for a person who is diagnosed with advanced cancer, d) home address is outside metropolitan areas, e) English speaking and f) able to consent. Exclusion criteria include (at the time of assessment for intake to the study): a) women who are cognitively impaired, as determined by the primary oncology or home care nurse; b) otherwise unable to participate, in the opinion of the nurse and; c) caring for a person who has advanced cancer and is also diagnosed with dementia. Male caregivers are excluded because caregiver appears to have a greater impact on the health of women compared to men [20].

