**Figure 2 F2:**
[figure not shown]
**Data Collection**.

The second visit is scheduled for 1 week after the first visit. During the second, third, fourth fifth and sixth visit data is collected as per the first visit except for the demographic form. Further, subjects are asked additional questions such as how much time they spent during the week on their hope activity. At the second visit journals are photocopied.

Each visit is about 1-1.5 hours at the maximum to prevent fatigue. A week before each visit a reminder card is mailed to the caregiver's homes. Three days before the scheduled visit the RA's will phone to remind subjects of the data collection visit. To encourage retention birthday cards, a fridge magnet with the Living with Hope Logo and a newsletter is mailed from the team.

The site collaborator is also notifying the RAs as soon as a caregiver becomes bereaved. Data collection is continuing through bereavement following a one month time lapse from the death of the care recipient if subjects have completed the LWHP. In our preliminary work with caregivers who are bereaved data collection has not caused distress. This is supported by another study whose bereaved caregivers reported benefits of participating within the first year following bereavement [25]. Data collection will take place over 28 months.

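### The grief comparison in Hypothesis 3.1 cannot separate bereavement from the change of questionnaire version, unless the two versions are score-equivalent, which the article does not state

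*Protocol article*

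**What the plan says.** Hypothesis 3.1 (Specific Aim #3, under Specific Aims and Hypotheses) predicts that "the pattern of change in scores (GSE, RGEI/NDRGEI, HHI, and SF 12 V2) from baseline will be significantly different" for active and bereaved caregivers at 3, 6 and 12 months. The Data Analysis section tests this with a two-factor repeated-measures ANCOVA that has a "between groups factor (non-bereaved versus bereaved) and a repeated-measures factor for time (3, 6, and 12 months"). The covariates are the care recipient's PPS and those caregiver demographics found to be correlated. Significance is set at p < .05, with post hoc tests after a significant F.

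Table 1 assigns active caregivers the "Non Death Version of the Revised Grief Experience Inventory (ND RGEI") and bereaved caregivers the RGEI. The other three scores named in the hypothesis (HHI, GSE and SF-12) use the same form in both columns.

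Enrolment requires that the woman is "caring for a person who is diagnosed with advanced cancer", and the Methods/Design section says: "Baseline hope, quality of life, loss/grief, and self-efficacy data will be collected before the subjects receive the LWHP".

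On follow-up after a death, the Data Collection section says: "Data collection is continuing through bereavement following a one month time lapse from the death of the care recipient if subjects have completed the LWHP".

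**The concern.** A change score is interpretable when both measurements are on the same scale. For grief that holds in only one of the two groups being compared. The active group's change stays within one version, while the bereaved group's change crosses from one version to the other. If the versions differ in average level or in spread, the ANCOVA will attribute that difference to bereavement.

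The hypothesis is non-directional, since the article says that the direction of any difference is unknown. An artefact of either sign could therefore be taken as support. A significant grief result might then be reported as a different pattern of change after bereavement when part or all of it is the questionnaire.

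**Working it through.** **No figure in the plan to reproduce.** The article gives no power or effect size for the grief contrast. Its stated requirement of 98 subjects belongs to the path model of Aim 1 and has no bearing here.

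**Step 1: which version each score uses.**

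| | Baseline | Follow-up | Change score |
|---|---|---|---|
| Active | NDRGEI | NDRGEI | NDRGEI − NDRGEI |
| Bereaved | NDRGEI | RGEI | RGEI − NDRGEI |

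The baseline column follows from the inclusion criteria and the timing of baseline. The follow-up column follows from Table 1.

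**Step 2: what the group contrast estimates.** Let *d* be the difference in level between RGEI and NDRGEI for the same underlying grief. The expected bereaved-minus-active difference in change is then (true difference) + *d*. At each follow-up, version and bereavement status are the same variable, so adjusting for PPS, demographics or the baseline score does not separate them.

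**Step 3: main effect and interaction.** For a caregiver already bereaved at 3 months, a constant offset adds (*d*, *d*, *d*) at 3, 6 and 12 months. It shifts the group main effect by *d* and cancels from the group-by-time term. For one bereaved between 3 and 12 months, the added pattern is (0, *d*, *d*) or (0, 0, *d*), which does not cancel. A difference in scale between versions would not cancel for anyone whose grief changes over time.

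**Step 4: how much an offset could matter.** The documents give no value for *d*, so the following is an illustration with assumed values. It uses a two-sided 5% normal-approximation test at a single visit, with true difference zero and *d* in SD of the change score:

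SE = √(1/n₁ + 1/n₂)

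P(significant) = Φ(*d*/SE − 1.96) + Φ(−*d*/SE − 1.96)

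| Active v bereaved | SE | *d* = 0 | 0.1 | 0.3 | 0.5 |
|---|---|---|---|---|---|
| 50 v 50 | 0.200 | 5% | 8% | 32% | 71% |
| 44 v 78 | 0.189 | 5% | 8% | 36% | 76% |
| 50 v 150 | 0.163 | 5% | 9% | 45% | 87% |
| 100 v 100 | 0.141 | 5% | 11% | 56% | 94% |

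Example, 44 v 78 at 0.3 SD: 0.3/0.189 = 1.59; Φ(1.59 − 1.96) = Φ(−0.37) ≈ 0.36. The second term is negligible.

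**Step 5: where the group sizes come from.** The 100 v 100 split is the plan's 200 subjects with half bereaved, and 50 v 50 is half of that in each group. The 50 v 150 split takes the home-care figure of 75% dead by 82.75 days. The 44 v 78 split is for the 3-month visit. It uses the Sample Size quartiles (25% dead at 13 days, 50% at 36, 75% at 82.75) and assumes a constant hazard between quartiles, with the last hazard carried on to day 91:

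- Alive at day 91: 0.25 × exp(−8.25 × ln 2/46.75) = 0.221, or 44 of 200.
- Bereaved and assessable, meaning a death after the 2-week LWHP and at least a month before the visit (days 14 to 61): 0.737 − 0.345 = 0.392, or 78 of 200.

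This applies times measured in palliative home care to time since enrolment and allows for no other attrition. Both are assumptions.

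**The case against.** The strongest objection is that the bias depends on something the documents do not show. The active form is presented as a version of the same inventory, and the article says measures were chosen with later bereavement in mind. If the versions are score-equivalent, the bias is nil. A condensed article may leave item overlap and scoring to a fuller document. This stands as a limit on certainty: a reader might infer that any grief difference found would be an artefact, and the documents do not support that. It does not dispose of the point, because the article itself fixes the version per group, the change from baseline and the between-group test, and claims no equivalence.

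The illustrative test is also not the planned ANCOVA. That stands too. The table describes the group contrast at one visit, and for women already bereaved at 3 months a constant offset leaves the interaction untouched.

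A reader might count every death by day 91 as an assessed bereaved caregiver, giving 44 v 156 and false-positive rates of 42% and 83% at 0.3 and 0.5 SD. The requirement to have completed the LWHP and the one-month lapse after death rule that count out.

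A reader might also see an error in Aim 1, where "Loss and Grief [Revised Grief Inventory (RGEI) or NonDeath RGEI (NDRGEI)] scores predict changes in hope" at weeks 1 and 2. Because of the one-month lapse, RGEI scores should not arise that early, so the extra label changes no result.

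Finally, Aim 3 is exploratory and the main hypothesis lies elsewhere. That limits the importance of the point, but Hypothesis 3.1 is still a formal test at p < .05.

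**Conclusion.** The point holds for the grief score in Hypothesis 3.1. Bereavement status is fully aliased with questionnaire version at follow-up, so the planned main effect is the sum of a bereavement difference and a version offset that these data cannot separate. The group-by-time term is affected through caregivers who switch version between 3 and 12 months, and more widely if the versions differ in scale.

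Size and direction are unknown. On the assumed offsets, the false-positive rate runs from about 8-11% at 0.1 SD to 71-94% at 0.5 SD, and is 5% if the versions are equivalent. Those figures rest on the assumed offset, a single-visit normal approximation and group sizes from 50 v 50 to 100 v 100.

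A reader might extend the problem to all of Hypothesis 3.1. Table 1 does not support that, since HHI, GSE and SF-12 use one form throughout.

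**What to change.** In the analysis for Specific Aim #3:

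- Remove the mixed RGEI/NDRGEI change score from the between-group test of Hypothesis 3.1.
- Report NDRGEI change from baseline within active caregivers.
- Report RGEI in bereaved caregivers as its own series from their first assessment after the death, without subtracting the NDRGEI baseline.
- Keep an active-versus-bereaved grief comparison only if it uses items and scoring common to both versions, with the evidence of equivalence cited.

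The tests for HHI, GSE and SF-12 stay as planned, and the Aim 1 wording needs no substantive change. No new data or visits are required. The cost is analysis-plan wording and, if equivalence cannot be shown, the loss of a formal active-versus-bereaved test for grief.
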